##### Domain of Psychosocial Variables

###### Quality of Life

The World Health Organization Quality of Life—BREF (WHOQOL-BREF) is an abbreviated quality of life instrument developed by the World Health Organization. It consists of 26 items that are answered in response scales ranging from 1 to 5, and it is based on a four-domain structure (physical, psychological, social, and environmental) (35, 36).

###### Resilience

The Connor–Davidson Resilience Scale (CD-RISC) is a widely used self-report consisting of a 25-item questionnaire for evaluating individual resilience. It is divided into four domains: tenacity, adaptability–tolerance, reliance on support from the outside, and intuition (37, 38).

###### Social Support

The Medical Outcomes Study (MOS) Social Support Survey consists of 20 self-reported items (39).

###### Quality of Life-Adjusted Years

The SF-6D was adapted to Brazilian Portuguese–Brazil (version 2002). This self-administered instrument produces a unique score, which ranges from 0 to 1. The score represents the strength of an individual’s preference for a given health condition; 0 corresponds to the worst health status and 1 corresponds to the best health status (40).

#### Confusion/Mediator/Moderator Factors

The mediating factors will be therapeutic alliance, motivation, and defense mechanisms (for PDT only). The moderating factors will be gender, age, religiosity, stressors, social support, personality traits, and defense mechanisms (for CBT and IPT). The confounding factors considered will be diagnosis, medication use, number of sessions, and comorbidities.

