## Aims

Our primary aim is to evaluate the outcomes associated with different forms of individual psychotherapy [psychodynamic psychotherapy (PDT), interpersonal psychotherapy (IPT), and CBT] in a public outpatient clinic for mental disorders. Our primary outcomes are divided into three domains of variables: clinical (general psychiatric symptoms), biological (serum BDNF levels), and psychosocial (resilience, quality of life, social support, and quality of life-adjusted years of life).

Our secondary aim is to evaluate potential confounders/mediators/moderators for the main outcomes: personality traits, type of psychotherapy, number of sessions, the therapist’s duration of training, concomitant use of pharmacological treatment, history of previous psychotherapeutic treatment, medical and psychiatric comorbidities, psychiatric diagnosis, therapeutic alliance, and defense mechanisms.

Our main hypothesis is that all three modalities of therapy will produce reduction of symptoms in the clinical domain and improvement in the psychosocial domain. All psychotherapies will increase BDNF at 6 months of follow-up. As secondary hypotheses, the mechanisms of improvement will be mediated by the therapeutic alliance, motivational status, and defense mechanisms (for PDT). The confounders of this therapeutic improvement will be number of sessions, comorbidities, and medication use. The moderating factors will be gender, age, personality traits, religiosity, and defense mechanisms (for CBT).

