#### Statistical Analysis

Shapiro–Wilk test will be used to determine normality. For parametric distributions, dependent or independent *t* tests will be performed. To determine differences between categorical variables, the chi-squared test will be used. For nonparametric distributions, we will use the Wilcoxon test and Mann–Whitney *U* test to compare nonrelated and related means, respectively. A generalized estimating equations (GEE) model will be used to investigate multivariate repeated measurements. The Hayes method will be used to analyze the mediators (52), and the multivariate regression will be used to analyze the confounders. *Post hoc* analyses will be performed using the Bonferroni test.

The data will be expressed as mean ± standard deviation (SD), and a *p* value less than or equal to 0.05 will be considered to be statistically significant (two-tailed). The statistical analyses will be performed using the SPSS version 20.0 software package (IBM^®^, New York, USA).

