Limitations of this study include the heterogeneity of the training and experience of the resident psychiatrists and the absence of evaluation from their point of view in the psychotherapeutic process. As a study is naturalistic, there is no way to control the impact of the researchers’ interviews. We will collect a series of demographic data, use of medications, and number of sessions to control possible confounders, but we know that because it is an open study, there is no way to control all differences between groups. Also, psychotherapy studies often have large amounts of losses (16). To control this bias, we will compare the clinical and demographic characteristics of the lost sample with those that continue in relation to the baseline. As for the multiplicity of diagnoses that may be found, to homogenize the sample, we will consider for inclusion the BDI value >15.

Studies such as this one seek to contribute to the foundations of public health policies and investments for the treatment of patients with severe mental illnesses who are at risk of hospitalization and suicide. These types of investigations also seek to promote mental health, rehabilitation, and social reintegration. Understanding the mediating and biological mechanisms of the psychotherapeutic process can help to optimize these interventions and facilitate their indication according to the psychopathological profile and the severity of the patients.

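### The mediator and moderator hypotheses fall under a blanket 0.05 rule with no multiplicity control, no order among themselves and no exploratory label, and the two moderator lists disagree

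*Protocol article*

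**What the plan says.** All references are to the protocol article.

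- **Rank.** Aims places this work below the main hypothesis: "Our secondary aim is to evaluate potential confounders/mediators/moderators for the main outcomes".
- **Mediators.** Aims states them as predictions: "As secondary hypotheses, the mechanisms of improvement will be mediated by the therapeutic alliance, motivational status, and defense mechanisms (for PDT". The later section on these factors agrees: "The mediating factors will be therapeutic alliance, motivation, and defense mechanisms (for PDT only".
- **Moderators.** Aims gives five: "The moderating factors will be gender, age, personality traits, religiosity, and defense mechanisms (for CBT". The later section gives seven: "The moderating factors will be gender, age, religiosity, stressors, social support, personality traits, and defense mechanisms (for CBT and IPT". It adds stressors and social support, and extends defense mechanisms from CBT to CBT and IPT.
- **Decision rule.** Under Statistical Analysis, a p "value less than or equal to 0.05 will be considered to be statistically significant (two-tailed". The rule is not limited to the main hypothesis. The only multiplicity adjustment stated is Bonferroni, for post hoc analyses. The Hayes method is named for mediators; no test is named for moderators.
- **Outcomes.** Table 1 lists eight instruments as primary: BDI, BAI, SCL-90-R, serum BDNF, WHOQOL-BREF, CD-RISC, MOS social support and SF-6D.
- **Use.** The Discussion closes by saying that understanding mediating and biological mechanisms can help to optimize the therapies and "facilitate their indication according to the psychopathological profile and the severity of the patients".

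**The concern.** The mediators and moderators are prespecified hypotheses, so a Bonferroni rule confined to post hoc analyses does not reach them, while the general 0.05 rule does. Read as written, every nominally significant mediator or moderator would be reported as a finding. Nothing says which of them matters most or that they only generate hypotheses.

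At stake is the credibility of statements about how these therapies work and for whom. The study is not randomised, has 126 patients, and was sized only on BDNF change. The defense-mechanism mediator applies to PDT alone, a group of 42 patients, or about 29 to 34 after the planned losses (42 × 0.70 = 29.4; 42 × 0.80 = 33.6). Settling the primary outcomes would not control this separate family.

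The disagreement between the two moderator lists adds to the problem, because an unsettled list leaves room to choose the family after the data are seen.

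**Working it through.** **The plan's own figure.** The article gives no familywise error rate for this family. Its one design figure is 42 per group, from a difference of 0.22, SD 0.43, 5% significance and 80% power. For a before-after change, n = (0.43 × (1.960 + 0.842) / 0.22)² = 29.98, so 30. Allowing for losses, 30 / 0.75 = 40 and 30 / 0.70 = 43, which bracket 42. The figure is reproduced, and it concerns BDNF change only. It does not address mediation or moderation.

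**Inputs for the error rate**
- Factors: 3 + 7 = 10 (section on confusion, mediator and moderator factors), or 3 + 5 = 8 (Aims).
- Outcomes: 1, or the 8 instruments of Table 1.
- Two-sided 0.05 per test (Statistical Analysis).
- Assumed: all nulls true, each test has exactly 5% type I error, each factor is counted once, and the correlation between test statistics lies between 0 and 0.7. The article gives no correlations.

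**Independent tests.** P(at least one false positive) = 1 − 0.95^m; expected number = 0.05 × m.

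| Factors × outcomes | m | P(at least one) | Expected |
|---|---|---|---|
| 8 × 1 | 8 | 33.7% | 0.4 |
| 10 × 1 | 10 | 40.1% | 0.5 |
| 8 × 8 | 64 | 96.2% | 3.2 |
| 10 × 8 | 80 | 98.4% | 4.0 |

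**Correlated tests.** Simulated as z_i = √ρ·z_0 + √(1 − ρ)·e_i, with z_0 and e_i independent standard normal, rejecting when |z_i| > 1.96 (200,000 draws for m = 10; 40,000 for m = 80).

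| ρ among all tests | m = 10 | m = 80 |
|---|---|---|
| 0.3 | 35% | 91% |
| 0.5 | 29% | 73% |
| 0.7 | 21% | 47% |

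If instead the ten factors are independent and only the eight outcomes are correlated, at 0.3, 0.5, 0.7 or 0.9, the 80-test figure is 97%, 94%, 88% or 72%. Correlation changes the chance of at least one error. It leaves the expected number at 4.

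**Sensitivity of the count.** Dropping the cell in which social support would moderate itself leaves 79 tests: 1 − 0.95^79 = 98.3%, expected 3.95. In the other direction, the article describes five personality domains, four motivation stages and two religiosity instruments. If each were tested separately, ten factors become 10 + 4 + 3 + 1 = 18 per outcome, and 1 − 0.95^18 = 60% for one outcome with independent tests.

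**The two lists side by side**

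| | Aims | Factors section |
|---|---|---|
| Gender, age, religiosity, personality traits | yes | yes |
| Stressors | no | yes |
| Social support | no | yes |
| Defense mechanisms as moderator | CBT | CBT and IPT |

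Social support is also a primary outcome, in Aims and in Table 1.

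**The case against.** The strongest reply is that this is a condensed article. Test lists and multiplicity rules for secondary analyses are commonly left to a full protocol or analysis plan, which is not shown. That is fair as far as a missing adjustment goes. But the article itself states a threshold without limits and an adjustment with limits, and together they define what will be called significant. The contradiction between the moderator lists is in the text and does not depend on any other document.

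A reader might also infer more than the documents support:

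- *That there is no hierarchy.* Aims ranks this work as a secondary aim with secondary hypotheses. Only an order within the set is missing.
- *That 80 tests are planned.* No test list is given. The 80 come from taking the main outcomes to be all eight instruments and using the longer moderator list; the shorter list gives 64.
- *That a false positive is likely on any given outcome.* For one outcome, with each factor counted once, the chance is 21% to 40%, below one half. Even across 80 tests it is 47% if all are correlated at 0.7.
- *That the results will decide who receives which therapy.* The Discussion says only that understanding mechanisms can help, does not name moderators and sets no rule. In this study, modality follows clinical judgment and the researchers take no part in it.

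The Discussion is also cautious elsewhere: it admits difficulty in separating mediators from confounders and says alliance may possibly mediate improvement. That caution fits exploratory work and supports saying so; it does not replace the label.

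**Conclusion.** The point holds in limited form. As written, the mediator and moderator hypotheses are judged at 0.05 each, with no control over the family, no order within it and no exploratory label.

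If every null is true, the chance of at least one false finding is 21% to 40% for ten factors on one outcome. It is about 47% to 98% if every factor is tested on all eight Table 1 instruments, with about four false findings expected. Both ranges rest on assumed correlations from 0.7 to 0 and on counting each factor once; the second also rests on a reading of the main outcomes. Some nulls are presumably false, so these are benchmark error rates and not forecasts.

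Separately, and without any assumption, the two moderator lists contradict each other, and social support is both a primary outcome and a moderator. The change is worth making because it alters what may be concluded at almost no cost.

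**What to change.** 1. In Aims, in the section on confusion, mediator and moderator factors, and in Statistical Analysis, label all mediator and moderator analyses exploratory. Report them as estimates with 95% confidence intervals, without significance claims.
2. Reconcile the moderator lists: whether stressors and social support belong, and whether defense mechanisms moderate in CBT only or in CBT and IPT. State that social support is not used as a moderator when it is the outcome.
3. In the Discussion, describe anything these analyses imply for the indication of therapy as hypothesis-generating.
4. Do not add a confirmatory mediation test, for example of therapeutic alliance, conditional on the main hypothesis being met, unless that hypothesis first has a success rule. In the article it spans three therapies, the clinical and psychosocial domains and BDNF, with no statement of what counts as success.

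The cost is wording only, since the same models are run on the same data. The downside is that mediators and moderators can no longer be reported as confirmed.

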**Methods:**
*Design:* longitudinal, naturalistic. *Participants:* One hundred twenty-six patients who underwent one of three evidence-based modalities of individual psychotherapy [psychodynamic psychotherapy (PDT), interpersonal psychotherapy (IPT), and cognitive–behavioral psychotherapy (CBT)] were included. *Measure:* Primary outcomes are divided into three domains of variables: clinical (general psychiatric symptoms), biological (serum BDNF levels), and psychosocial (resilience, quality of life, coping strategies, social support, and quality of life-adjusted years of life). Confounding/mediator variables included clinical (personality traits, type of psychotherapy, number of sessions, concomitant use of pharmacological treatment, history of previous psychotherapeutic treatment, medical and psychiatric comorbidities, and psychiatric diagnosis), psychosocial (psychosocial stressors, therapeutic alliance, and defense mechanism style), and other (religiosity) factors. *Procedure:* The follow-up period will be baseline and 6 months and 1 year after entering the study. The study will include 42 controls for biological variables only. Sample size calculation considered a significance level of 5% and a power of 80% to detect a difference of 0.22 with a standard deviation of 0.43, assuming losses of 20–30% of patients. The comparison between the modalities of psychotherapy will be by generalized estimating equations (GEE) model, the analysis of mediators by the Hayes method, and confounders by multivariate logistic regression.

**Discussion:** The findings of this study are intended to demonstrate the outcomes of evidence-based psychotherapies for clinical, psychosocial, and biological parameters and to understand the mediators and confounders of this process in a real-life setting for patients with severe mental illness, thus contributing to the establishment of evidence-based public health policies in the field of psychological interventions.

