### Participants

All patients included at the HCPA psychotherapy clinic will be evaluated by a fourth-year psychiatry resident with training in psychotherapy. Patients will be referred from the outpatient clinic of clinical psychiatry, pain medicine, or preoperative bariatric surgery. Each patient who agrees will undergo up to five evaluation interviews and engage in discussions with a supervisor. They will be next referred, based on clinical judgment, to the most suitable modality of psychotherapy. The clinic offers three methods of individual psychotherapy: PDP, IPT, and CBT.

The psychotherapy modality will be indicated by general criteria (17), considering the following characteristics: previous favorable experience with some kind of psychotherapy, psychological-mindedness, presence of personality disorder or traits, number of diagnoses of psychiatric disorders, and relief of symptoms. When diagnosed with personality disorder associated with one or more major psychiatric disorders and psychological-mindedness, PDT will be indicated. When there are up to two major psychiatric diagnoses without personality disorder, it will be directed to CBT as well as in the exclusive quest for symptom relief. When the focus of the problem is exclusively up to two of the following: 1) dispute, 2) roles dispute, 3) role transition, or 4) interpersonal deficits and no personality disorder, IPT will be indicated.

Psychotherapeutic care will be provided by psychiatry residents in their second, third, and fourth years of residency in psychiatry under weekly supervision of dialogued interviews. The residents have weekly theoretical seminars related to each of the psychotherapeutic techniques offered throughout the period of residence. They also engage in weekly clinical seminars in which patients are interviewed by teachers to prompt discussions about the clinical aspects related to cases. When there is doubt about patient management, the patient is interviewed by the supervisor.

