2.1 Clinical domain			
Diagnosis (review of medical records)	X		
Psychodynamic Diagnosis (OPD-II)	X	X	
			
Comorbidities	X		
Pharmacological treatment	X	X	X
Personality traits (PID-V)	X		X
Number of sessions		X	X
Type of psychotherapy	X		

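### Number of sessions accrues after the modality is chosen, yet it is classed as a confounder; controlling for it would distort the comparison of modalities

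*Protocol article*

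**What the plan says.** The role of number of sessions is stated in three places in the Protocol article, and they agree.

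- Aims: "The confounders of this therapeutic improvement will be number of sessions, comorbidities, and medication use".
- Confusion/Mediator/Moderator Factors: "The confounding factors considered will be diagnosis, medication use, number of sessions, and comorbidities". The same paragraph lists mediators and moderators separately, and sessions are in neither list.
- Discussion (limitations): "We will collect a series of demographic data, use of medications, and number of sessions to control possible confounders".

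On timing, the Table 1 row "Number of sessions" is marked at 6 and 12 months and has no baseline mark. Modality is settled earlier, after the evaluation interviews (Participants): "They will be next referred, based on clinical judgment, to the most suitable modality of psychotherapy".

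On analysis, the Abstract says: "The comparison between the modalities of psychotherapy will be by generalized estimating equations (GEE) model". For confounders, Statistical Analysis says "the multivariate regression will be used to analyze the confounders"; the Abstract calls this regression logistic. The primary aim is to evaluate the outcomes associated with each form of psychotherapy. No direct effect and no per-session effect is named as a target.

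**The concern.** A confounder of the modality comparison has to influence, or share a cause with, both the choice of modality and the outcome. Sessions attended cannot influence a choice made before they took place. They are the amount of treatment received, and plausibly depend on which modality was chosen, how the alliance developed, how the patient responded and whether the patient dropped out.

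Two things follow if the comparison of modalities controls for sessions. First, any benefit that a modality delivers by keeping patients in therapy longer is taken out of its estimated effect. Second, patients who stop early because they are well and those who stop early because they are not improving receive the same covariate value. Conditioning on that value can link modality to unmeasured causes of outcome and create a difference where none exists.

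**Working it through.** **Step 1: the order of events.** Evaluation interviews come first, then referral to a modality (Participants). The baseline assessment follows, no later than the fourth session (Design). Sessions are recorded at 6 and 12 months (Table 1). The count therefore comes after the exposure. Table 1 places it under a joint heading for confounders and mediators, but Aims and Confusion/Mediator/Moderator Factors settle the role as confounder. The Discussion admits that mediators and confounders were hard to tell apart, but does not change that role.

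**Step 2: what controlling for it does.** The plan gives no figure for sessions by modality or for the effect of sessions on outcome, so there is no plan figure to reproduce. The following only illustrates the mechanism; every path value is an assumption.

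Let T be modality (0 or 1), S sessions, Y outcome and U an unmeasured cause of S and Y. U and both error terms have variance 1, and U is independent of T:

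- S = a·T + u·U + error
- Y = c·T + b·S + v·U + error

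The total effect of modality is c + a·b. The coefficient of T after adjustment for S is c − v·a·u/(u² + 1).

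| Case | a | b | c | u | v | Total effect | Adjusted for S |
|---|---|---|---|---|---|---|---|
| (a) part of the effect runs through sessions | 0.6 | 0.5 | 0.2 | 0 | 0 | 0.2 + 0.30 = 0.50 | 0.20 |
| (b) all of it runs through sessions | 0.6 | 0.5 | 0 | 0 | 0 | 0.30 | 0.00 |
| (c) as (a), with an unmeasured common cause | 0.6 | 0.5 | 0.2 | 0.5 | ±0.5 | 0.50 | 0.2 ∓ 0.12 = 0.08 or 0.32 |
| (d) no effect at all, with an unmeasured common cause | 0.6 | 0 | 0 | 0.5 | ±0.5 | 0.00 | ∓0.12 |

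The 0.12 is 0.5 × 0.6 × 0.5/(0.25 + 1). A simulation with 400,000 patients agreed: adjusted values were 0.197 in (a), 0.002 in (b), 0.072 and 0.320 in (c), and −0.119 and +0.124 in (d). The unadjusted estimates were within 0.003 of the total effect in every case.

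**Step 3: when the problem disappears.** With a = 0 the total effect is c and the adjusted coefficient is also c. Both biases in the modality contrast therefore require modality to change the number of sessions. Loss of a true effect also requires sessions to change the outcome.

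The illustration leaves out confounding by indication, which this non-randomised study also has. That problem calls for adjustment for variables measured before treatment, and a post-treatment count does not supply it.

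**The case against.** The strongest reply is that the article never says sessions enter the main comparison. GEE is assigned to the modalities and a separate regression to the confounders, and an article commonly leaves covariate lists to the full protocol or analysis plan. This stands in part. A reader might infer that the GEE model is adjusted for sessions as a fixed matter, and the text does not establish that. What it does fix is the label of confounder, given twice, and the purpose of control. Anyone who carries out the plan as worded would be led to adjust.

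Several stronger readings are tempting and are not supported:

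- **A percentage loss of the planned effect.** A reader might set an assumed path through sessions against 0.22/0.43 = 0.51 SD from Sample Size Estimation. That figure rests on BDNF before and after psychotherapy. A paired calculation, (0.43 × 2.80/0.22)² ≈ 30, or 43 after 30% losses, comes close to the stated 42, whereas a two-sample calculation needs 60 per group before losses. It is best read as a within-group change, so it is the wrong denominator for a contrast between modalities.
- **Bias in the within-group improvement.** The main hypothesis is that patients improve under all three modalities. Whether a session covariate would absorb that change depends on how it is coded, which is not given.
- **Medication as the same error.** Medication is also recorded at baseline, and the article does not say which value is used. Medication changes during follow-up are a rival explanation for change from baseline, so whether to account for them is a trade-off.
- **Type of psychotherapy as a confounder.** It appears only in lists with mixed headings, such as the Abstract's "clinical (personality traits, type of psychotherapy, number of sessions, concomitant use of pharmacological treatment", and not in the two lists that assign the confounder role.
- **Social support as both outcome and moderator.** It has a baseline value that can moderate other outcomes, and nothing says that it will moderate itself.

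**Conclusion.** The concern holds in a limited form. Number of sessions is wrongly classed: it follows the choice of modality and is part of the treatment received, so it is not a confounder of the modality comparison. If it is controlled for there, the estimate no longer answers the primary aim, read as the total outcome associated with each modality. Adjustment would suit only a direct or per-session effect, which the aims do not name.

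The size of the distortion cannot be derived from the documents. On the assumed paths it ranges from nil (modality does not affect sessions) to complete removal of the effect (all of it runs through sessions), and a spurious difference of about 0.12 can arise where there is no effect. The conclusion about the label is firm. That the main model would include sessions is an inference, though the wording points that way.

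**What to change.** In Aims, in Confusion/Mediator/Moderator Factors and in the limitations paragraph of the Discussion, take number of sessions off the list of confounders to be controlled. State that the primary comparison of modalities is adjusted for pre-treatment covariates: baseline diagnosis, comorbidities, baseline medication and the variables that guide the choice of modality (Participants). Analyse sessions as a dose or mediator variable in a separate, clearly secondary analysis. An analysis that accounts for medication changes during follow-up can be kept as a sensitivity analysis.

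The cost is a change of wording and one separately labelled analysis. Table 1 can keep its collection of sessions at 6 and 12 months, and the sample size does not change.
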